## Abstract

**Background:**

Modified *Sijunzi* decoction (SJZD) has been used to treat ulcerative colitis (UC) in remission. However, more rigorous clinical trials are necessary to evaluate its effectiveness. Therefore, a series of single-case randomised controlled trials (*N*-of-1 trials) is proposed to compare the efficacy of modified SJZD with mesalazine for treating UC in remission.

**Methods:**

This is a single-site, hospital-based, double-blind *N*-of-1 trial for 10 single subjects. Three cycles of *N*-of-1 trials are planned. There are two treatment periods in each cycle. Modified SJZD combined with mesalazine placebo or mesalazine combined with modified SJZD placebo will be randomised during each 8-week treatment period. There is no washout period in the study. Subjects will be selected by the researcher strictly in accordance with the inclusion and exclusion criteria.

**Discussion:**

Paired *t* tests and mixed-effect models will be used to analyse the visual analogue scale (VAS) for clinical symptoms and the quality of life questionnaire responses. The findings will be interpreted with caution. We anticipate that the results will show that modified SJZD is effective for patients with UC in remission.

**Trial registration:**

Chinese Clinical Trial Register, ID: ChiCTR1900024086. Registered on 24 June 2019.

## Background

Ulcerative colitis (UC) is a chronic, relapsing inflammatory bowel disease that is localised to the colonic mucosa and has an unknown aetiology. Its main clinical manifestations include bloody stools, diarrhoea, and abdominal pain [1]. The incidence of UC ranges from 0.42 to 4.6 per 100,000 people-years in Eastern Asia, while the incidence in Western countries remains high as prevalence surpasses 0.3% [2]. It is anticipated that the incidence difference between Eastern and Western countries will decrease [3–5]. UC is a complex and costly disease affecting the productivity and quality of life (QOL) of patients, which incurs a significant economic and mental burden.

The long-term pharmacological treatment for UC in remission includes 5-aminosalicylic acid (5-ASA), corticosteroids, and immunosuppressant agents. 5-ASA, also known as mesalazine, is generally used as a first-line treatment for patients with mild to severe UC [6]. Mesalazine is recommended by the Asia Pacific Association of Gastroenterology (APAGE) for the treatment of UC in remission [6]. However, a subpopulation of patients is intolerant or refractory to mesalazine or unable to tolerate the adverse effects of this therapy, resulting in increased susceptibility to infection and the production of low responders [7]. Traditional Chinese medicine (TCM) has been used to treat UC as an adjunctive or alternative therapy, and has had a positive impact on improving patients’ clinical symptoms and QOL through the relief of abdominal pain, diarrhoea, and inflammation [8–10].

*Sijunzi* decoction (SJZD) is the basic formulation of TCM for strengthening the spleen and replenishing *qi*. Modified SJZD is based on SJZD and adds another Chinese medicine to treat the specific symptoms of UC [11]. SJZD or modified SJZD has been widely used to treat patients with UC in remission [12–15]. Experimental research has identified numerous pharmacological effects of SJZD, such as promoting digestion and absorption, regulating gastrointestinal motility, creating resistance to gastrointestinal mucosal injury and enhancing intestinal mucosal immunity [16–19]. There have been several clinical observations using modified SJZD independently to treat UC in China that have reported that modified SJZD was effective [20–23]. However, because of the risks of bias reported in those clinical studies, further clinical evidence and rigorous randomised controlled trials (RCTs) are needed to confirm the results.

### Rationale for using *N*-of-1 trials

A series of *N*-of-1 trials was chosen for the following reasons:
UC is characterised by repeated relapse and remission [1]. A realistic treatment approach is to maintain remission for a long period after remission induction [1]. Patients need personalised treatment to alleviate prolonged suffering. UC meets the required conditions of *N*-of-1 trialsRCTs are not suitable for all diseases and treatments. *N*-of-1 trials can be considered for nonprogressive chronic disease [24, 25]. The *N*-of-1 trial is designed for a single patient or a series of individual patients. Multiple randomised crossover trials are alternated between the intervention period and the control period [26, 27]. *N*-of-1 trials have been placed at the pinnacle of the evidence hierarchy by the Oxford Centre for Evidence-Based Medicine, with the systematic review of RCTs being in second place [28]. Compared with RCTs or crossover trials, *N*-of-1 trials have higher power and require smaller sample sizes [29]*N*-of-1 trials meet the characteristics of syndrome differentiation and the individual medical interventions in TCM. Different interventions can be set up for each patient, and this design can provide a more flexible clinical trial design for TCM

### Objectives

This study aims to compare the efficacy of modified SJZD with mesalazine to treat patients with UC in remission using a series of *N*-of-1 trials.

## Methods

### Trial design

Three cycles of *N*-of-1 trials were chosen for the following reasons: (1) *N*-of-1 trials generally involve three or more cycles. Three cycles are the most commonly planned number of treatment cycles [30] and (2) for *N*-of-1 trials, the number of cycles is a variable in the sample size calculation [29]. Different cycles result in different sample sizes. Longer cycles will result in a higher dropout rate.

The *N*-of-1 trials will consist of three cycles, each cycle comprising 8 weeks of an intervention period and 8 weeks of a control period, in a random order. There is no washout period in this study. The protocol conforms to the Standard Protocol Items: CONSORT extension for reporting *N*-of-1 trials (CENT) 2015 [26]. Table 1 shows the schedule of enrolment, interventions, and assessments.

**Table 1 Tab1:** Schedule of enrolment, interventions, and assessments

Time point		Enrolment	Allocation	Cycle1		Cycle2		Cycle3		Close-out
				Weeks1–8	Weeks9–16	Weeks17–24	Weeks25–32	Weeks33–40	Weeks41–48	
Enrolment	Eligibility screen	**X**								
	Informed consent	**X**								
	Allocation		**X**							
Intervention	Modified *Sijunzi* decoction combined with mesalazine placebo or mesalazine combined with modified *Sijunzi* decoction placebo			**X**	**X**	**X**	**X**	**X**	**X**	
Assessment	Laboratory tests	**X**		**X**	**X**	**X**	**X**	**X**	**X**	**X**
	Vital signs	**X**		**X**	**X**	**X**	**X**	**X**	**X**	**X**
	Adverse events			**X**	**X**	**X**	**X**	**X**	**X**	
	VAS (abdominal pain, diarrhoea, bloody stool, mucus stool), stool frequency, SIBDQ, RFIPC, SHS, and TCM syndrome scale	**X**		**X**	**X**	**X**	**X**	**X**	**X**	

*RFIPC* Rating Form of Inflammatory Bowel Disease Patient Concerns*, SHS* Short Health Scale*, SIBDQ* Short Inflammatory disease Patient Concerns, *TCM* traditional Chinese medicine, *VAS* visual analogue scale

### Participants

All UC patients will be enrolled from the First Affiliated Hospital of Guangzhou University of Chinese Medicine (GZUCM). Ethical approval was obtained from the Ethics Committee of The First Affiliated Hospital of GZUCM.

The patients will be included if they meet the following inclusion criteria:
Patients diagnosed with UC in the remission phase (determined by a UC Disease Activity Index score of 0–2 and a bloody stool score of 0) according to ‘The Asia-Pacific consensus on ulcerative colitis’ promulgated by APAGE on Inflammatory Bowel Disease in 2010 [6]Patients diagnosed with dampness, stagnancy, and spleen deficiency syndrome according to ‘The experts of TCM consensus on ulcerative colitis (2017)’ promulgated by the Spleen and Stomach Diseases Branch of the Chinese Society of TCM [11]. The symptoms included abdominal distension and pain, relatively high frequency of stool, production of thin faecal matter, a red and white, sticky, jelly-like stool or indigested food in the stool, pale complexion, mental fatigue, pale tongue with greasy coating (moss), and weak pulsePatients aged between 18 and 75 yearsPatients who agree to voluntary participation in this study, sign the informed consent form, and have good compliance

The patients will be excluded according to the following criteria:
Patients with active UC, severe UC, or the acute fulminating type of UCPatients undergoing treatment with corticosteroids (orally administered, enemas, suppository, or injectable solution)Patients treated with blood-cell apheresisPatients who were administered anti-tumour necrosis factor-a antibody within 90 days before starting the study drugPatients with a history of hypersensitivity to mesalazine and salicylic acidPatients with serious cardiovascular disease, haemodyscrasia, or lung disease or with a history of these conditionsPatients with liver disease or kidney diseasePatients with a malignant tumour as a complication;Pregnant women or those who are breastfeeding

Patients will be withdrawn from the trials if they meet the following criteria:
Patients whose symptoms worsen and whose Mayo Disease Activity Index score (Mayo scores) increase by ≥ 30% during the treatment, compared with the baselinePatients with serious adverse reactions during treatment, or patients who voluntarily quit or are found to be ineligible for the study by the investigatorsPatients whose total medication that is not within 80 to 120% of the total required amount of medication after the trialPersonal patient request for withdrawal due to health considerations or a withdrawal request by the investigator

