### Outcomes

The primary outcomes for this trial are the changes in the visual analogue scale (VAS) for diarrhoea, abdominal pain, mucus in the stool, and bloody purulent stool. The secondary outcomes will include the TCM syndrome scale, the Short Inflammatory Bowel Disease Questionnaire (SIBDQ), the Rating Form of Inflammatory Bowel Disease Patient Concerns (RFIPC), and the Short Health Scale (SHS). Efficacy indicators for each subject will be observed and recorded before the study and at the end of each period (including week 8, week 16, week 24, week 32, week 40, and week 48).

Patients will be asked to rate their diarrhoea, abdominal pain, mucus in the stool, and bloody purulent stool severity by placing a vertical mark on a 10-mm horizontal VAS. The left and right extremes of the VAS are labelled ‘the lightest’ and ‘the most serious’, respectively.

The (TCM) Traditional Chinese medicine syndrome scale is an efficacy evaluation of six items measuring dampness, stagnancy due to spleen deficiency syndrome: diarrhoea, bloody purulent stool, anorexia, abdominal distension, limb burnout, and disinclination to talk due to mental weariness. Each item is rated from 0 to 3. The higher the scale, the more serious is the dampness stagnancy [11].

The SIBDQ uses 10 items derived from the inflammatory bowel disease questionnaire, which explain 90% of the variance in the SIBDQ for UC patients. The total score ranges from 10 (worst health) to 70 (best health). This gauge of subjective health status or quality of life in patients can be administered and scored quickly and easily [31].

The RFIPC is a self-administered form containing 25 items of concern related to inflammatory bowel disease. Each item is rated from 0 to 100 on a VAS form. The average score of all 25 items is the ‘sum score’. A higher score indicates a higher level of patient anxiety [32].

The SHS is a disease-specific questionnaire consisting of four items measuring four dimensions of health: bowel symptom severity, social functioning in daily life, disease-related worry, and perceptions of general well-being. Item responses are indicated on a 100-mm VAS from 0 to 100. The higher the scale, the more serious are the health concerns [33].

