## Discussion

A sufficient washout period is necessary for *N*-of-1 trials because the latter intervention may be affected by the carryover effects of the previous intervention. However, the patient does not receive effective treatment during washout periods. Therefore, including a washout period would be inappropriate for UC patients. For patients with UC in the remission phase, insufficient treatment leads to acute UC or aggravation of UC [36, 37]. Therefore, there are no washout periods in our study.

Although there are no washout periods in this study, we considered that the carryover effects of modified SJZD have little effect in practice. The reasons are as follows: (1) the main active ingredients of SJZD are glycyrrhizic acid, glycyrrhetinic acid, pachymic acid, atractylodes lactone III, ginsenoside Re, and ginsenoside Rb_1_, and a pharmacokinetic study showed that their mean half-life is no more than 12 h [38]. For the other active ingredients of modified SJZD, further studies reported that their half-life is no more than 24 h [39–45] and (2) even if there are carryover effects for modified SJZD, a mixed-effect model will be used to analyse the data from the *N*-of-1 trials. The mixed-effects model can estimate treatment effects accurately while controlling for carryover effects; it separates carryover effects from treatment effects in a series of *N*-of-1 trials [34].

The Mayo score is a general indicator used to assess the severity of active UC [6]. If the procedure for calculating the Mayo score is followed properly, the patients with UC would undergo enteroscopy after each period (one per month in the trial). This would be too frequent for patients to accept. Therefore, the Mayo score will not be used as the primary outcome. Diarrhoea, abdominal pain, and mucus in the stool are the most common symptoms for patients with UC. Bloody purulent stool was reported to have a close relationship with clinical relapse [46, 47]. For these reasons, the VAS scores for the main clinical symptoms (diarrhoea, abdominal pain, mucus in the stool, and bloody purulent stool) were chosen as the primary outcomes.

Our findings will be interpreted with caution. We anticipate that the results will show that modified SJZD is effective for patients with UC in remission.

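### The worsening-withdrawal rule has no consistent index, baseline or scoring time; mid-period withdrawal leaves the failed period unscored; and the adherence rule can act only after completion

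*Protocol article*

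**What the plan says.** **Entry (Participants).** Remission is defined by "a UC Disease Activity Index score of 0–2 and a bloody stool score of 0".

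**Withdrawal (Participants).** The list opens with "Patients will be withdrawn from the trials if they meet the following criteria". Its first item covers "Patients whose symptoms worsen and whose Mayo Disease Activity Index score (Mayo scores) increase by" 30% or more relative to baseline. A later item covers patients whose total medication falls outside 80–120% of the required amount, judged when the trial is over. Patients may also leave at their own or the investigator's request.

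**Schedule (Trial design, Table 1).** The efficacy row reads "VAS (abdominal pain, diarrhoea, bloody stool, mucus stool), stool frequency, SIBDQ, RFIPC, SHS, and TCM syndrome scale". No row names a Mayo score, a UC Disease Activity Index or an endoscopy, at enrolment or in any period. There is an eligibility-screen row at enrolment.

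**Timing (Outcomes).** Efficacy indicators are "observed and recorded before the study and at the end of each period", that is, at weeks 8, 16, 24, 32, 40 and 48.

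**Feasibility (Discussion).** With proper Mayo scoring, "the patients with UC would undergo enteroscopy after each period (one per month in the trial"; the article adds: "This would be too frequent for patients to accept". It concludes that Mayo will not be the primary outcome.

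**Analysis (Statistical methods).** Pooled data are analysed by a paired t test and also by a mixed model.

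**The concern.** The withdrawal rule needs three things: a named index, a baseline value and a later value. The article gives one index name at entry and another at withdrawal, schedules neither, and argues against routine collection of the one that withdrawal depends on. The percentage is also a poor fit if the baseline lies between 0 and 2.

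This matters statistically because worsening is what a remission trial is meant to detect. If a patient leaves in the middle of a period because a treatment is failing, and scores exist only at period ends, the most informative observation is never made. The comparison then rests more heavily on periods that went well.

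The adherence rule raises a related problem. A patient who has completed all six periods can no longer be withdrawn from treatment. The only thing left to remove is the patient's data, on the basis of behaviour after randomisation.

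**Working it through.** **1. The 30% rule against the entry range.** Inputs: entry index 0–2 and a relative rise of at least 30% (both Participants). Assumptions: the two names denote one index, and it is scored in whole points. Relative rise = (new − baseline) / baseline.

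| Baseline | 30% of baseline | Smallest possible rise | As a percentage |
|---|---|---|---|
| 0 | 0 | 1 point | 1/0, undefined |
| 1 | 0.3 points | 1 point | 1/1 = 100% |
| 2 | 0.6 points | 1 point | 1/2 = 50% |

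Under this reading the 30% figure never separates a qualifying rise from a non-qualifying one.

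**2. The other reading.** If the indices differ, the table does not apply, because the Mayo baseline need not be 0–2. But then no Mayo baseline is scheduled. The eligibility screen would supply only the entry index. The two faults are alternatives and do not add up. Under either reading, no later value is scheduled.

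**3. What a mid-period withdrawal leaves.** Scores are taken only at period end.
- Failure in the second period of a cycle: the first period has a score and the second does not. The paired test loses the cycle. The mixed model keeps the first score but lacks the failed one.
- Failure in the first period of a cycle: neither period has a score, and both analyses lose the cycle.

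Later cycles do not take place in either case.

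**4. Direction of the effect (illustration only).** Assumptions: independent normal period scores, SD 0.8 and difference 0.7 (Sample size), means 0.7 (worse treatment) and 0 (better), and any score above a cut-off c missing. The mean of the retained scores is μ − σφ(a)/Φ(a), with a = (c − μ)/σ.

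| c | Lost, worse / better treatment | Retained difference |
|---|---|---|
| 2.0 | 5% / 1% | 0.62 |
| 1.5 | 16% / 3% | 0.53 |
| 1.0 | 35% / 11% | 0.40 |

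For c = 1.5: worse treatment 0.7 − 0.8 × 0.242/0.841 = 0.470; better treatment 0 − 0.8 × 0.069/0.970 = −0.057; difference 0.53. The cut-offs are invented and are not the protocol's trigger. Other assumed set-ups gave values up to 0.68. All shrink the difference, but the size follows from the assumptions.

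**5. The planned sample size and its margin.** n = 2 × SD² × (1.960 + 0.842)² / (3 × 0.7²) = 1.28 × 7.849 / 1.47 = 6.83. With a noncentral t (3n − 1 degrees of freedom), 7 patients give about 77% power and 8 give 82.7%, so the stated 8 reproduces; 8/0.8 = 10. The allowance therefore covers 2 of 10 patients. If removed patients contributed nothing, a third removal would leave 7 and about 77% power. The documents give no removal rate. At assumed rates of 10%, 20%, 30% and 40%, the chance of losing three or more of ten is 7%, 32%, 62% and 83%.

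**6. The adherence rule.** It uses total medication over the trial. A patient taking 100% in one treatment's periods and 60% in the other's averages (100 + 60)/2 = 80% and passes.

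**The case against.** A reader might infer that the worsening rule cannot be applied at all. The documents do not support that. Even with a baseline of 0–2, the percentage is undefined only at 0. Worsening symptoms are also required, so the percentage is not the sole trigger. The Discussion objects to routine scoring after every period and rules Mayo out only as primary outcome; it does not forbid scoring a patient who gets worse. The two names may denote one instrument, in which case the eligibility screen supplies a baseline.

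A reader might also infer that failed periods are deleted from the comparison. Nothing says that recorded data are discarded. Analysis sets and missing-data handling may sit in an analysis plan that is not shown, and the mixed model can use completed periods from unfinished cycles. What remains is narrower: no analysis plan can restore a score that the schedule never collects.

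Nor does the adherence rule select patients who took both treatments well, as step 6 shows, and no adherence rate is given from which to say that it exhausts the 20% allowance.

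The monthly count in the Discussion conflicts with 8-week periods. That is a separate slip and adds nothing to the withdrawal argument.

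**Conclusion.** The point holds as an inconsistency with a statistical consequence. The entry criterion, withdrawal criterion, schedule and Discussion do not agree on which activity index is used, what its baseline is and when it is scored. On the one-index reading, assuming whole points, the 30% figure is undefined at 0 and met by any 1-point rise at 1 or 2. On the two-index reading, no Mayo baseline is scheduled.

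Mid-period withdrawal for worsening leaves the failed period without a score. The likely direction is toward a smaller treatment difference, provided that failure is more common on one treatment and the score is missing. The size cannot be estimated from the documents, and the figures in step 4 show direction only. The adherence rule, as timed, can work only as a post-randomisation exclusion of patients who have finished.

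**What to change.** - Reconcile the inclusion criterion, the withdrawal criterion, Table 1 and the Discussion on which index is used, what its baseline is and when it is scored. Any clinical threshold is for the sponsor's clinicians. Correct the monthly count in the same pass.
- Record the VAS items and questionnaires at the time of withdrawal, with the date and the treatment period.
- State that all recorded periods stay in the mixed model, including those from unfinished cycles.
- Report withdrawals for worsening by the treatment being taken.
- Use 80–120% adherence only to define a sensitivity set, not as a ground for withdrawal.

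The cost is amendment wording and one set of self-rated forms per withdrawal, with no extra patients. The small downside is that a withdrawal score reflects less than 8 weeks of exposure, so the report should identify such scores.

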### Interventions

Patients in the intervention period will be treated with 300 ml modified SJZD granules and 1 g mesalazine placebo three times each day, while patients in the control period will be given 1 g mesalazine three times and 300 ml modified SJZD granules placebo each day. Each period lasts for 8 weeks.

Modified SJZD is a combination of *Radix pseudostellariae* (*Taizishen*), *Atractylodes macrocephala* (*Baizhu*), Poria (*Fuling*), *Portulaca oleracea* L (*Machijian*), *Rhizoma cimicifugae* (*Shengma*), *Citrus aurantium* L (*Zhike*), and *Agastache rugosa* (*Huoxiang*). If the symptom of bloody purulent stool is severe, *Polygonum chinense* L (*Huotanmu*) and *Crinis carbonisatus* (*Xueyutan)* will be added. If the symptoms of tenesmus are severe, *Verbena officinalis* L (*Mabiancao*), *Paris yunnanensis* Franch (*Chonglou*), and *Indigo naturalis* (*Qingdai*) will be added. All ingredients will be manufactured as a Chinese herbal granule by Guangdong Yifang Pharmaceutical Co. Ltd. Mesalazine enteric-coated tablets ([name] GmbH, Freiburg, Germany) will be used in the study. Guangdong Yifang Pharmaceutical Co. Ltd. makes both of the placebos, which have an identical shape, colour, and weight as the active drugs.

